### Statistical Analysis

The calculation of the sample size was done with respect to the primary endpoint and the primary analysis. Using the exact binomial test, we aim to show that the primary endpoint is reached at values of ≥80% of all study subjects answering ≥80% of the app-based questions during their radiotherapy as outpatients. With a sample size of 50 patients in this pilot study and an assumed percentage of 92% for the primary endpoint, a power of 1-β=80% is reached with a one-sided significance level of α=5%. Considerations regarding sample size and power were done using the *PROC POWER* procedure in SAS (version 9.4). The primary endpoint will be evaluated using the exact binomial test, which is the primary analysis. The one-sided significance level for this feasibility study is set to 5%.

Methods of descriptive data analysis will be used to describe patient characteristics and secondary outcomes, including calculation of appropriate summary measures of the empirical distribution, such as mean and standard deviation, median and interquartile range for continous variables, as well as absolute and relative numbers for categorical variables. Additionally, according to tumor type, subgroup analyses will be performed as a sensitivity analysis. Additionally, multivariable regression models will be used to analyze the relationship between patient characteristics and the primary endpoint. However, we will consider the primary variable on the original scale without any cut-off value (ie, the relative number of app-based answered questions) as the outcome variable and, thus, linear regression models will be applied. Age, gender and the need of toxicity-caused hospitalization will be included as predictors. The same model will be applied for the secondary endpoints. In addition, correlations will be considered. Graphical methods will be applied to visualize the results.

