## Methods

### Study Design

The present study is designed as a prospective, single-center pilot study and will be conducted at Heidelberg University Hospital’s Department of Radiation Oncology. Cancer patients undergoing radiotherapy are offered a novel model of therapy support during the course of treatment, where a mobile app will be used to monitor patient-reported outcomes concerning general performance and therapy-related symptoms, and enable patients to express the need to see a physician when clinical symptoms occur. The length and frequency of consultations with a physician will be analyzed to assess the economic aspect of the model. Furthermore, the necessity of admitting a patient to inpatient care during the course of therapy will be documented together with the timepoint of admission. Since routine bloodwork is independently conducted at regular intervals for all patients undergoing radiotherapy, the data from this bloodwork together with the clinical parameters documented in this study (eg, symptoms, toxicity, etc) will be screened for predictive factors for the necessity of inpatient admission by means of correlation. This is done as part of an exploratory side analysis unrelated to the primary objective of this study.

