**Figure 2 figure2:**
[figure not shown]
Sample screenshot of the mobile application for patient support during radiotherapy.

For example, patients are asked to describe their general health/QoL subjectively on a 7-point scale covering a range from “excellent” to “very poor” (adapted from EORTC QLQ-C30). Furthermore, patients are asked to state whether or not they feel the need to personally consult a physician on that respective treatment day. If they do, upon completing the survey, an automatic notification is triggered at the medical-technical assistants’ management terminal, prompting them to schedule a visit with the supervising physician on that day. The information provided via the survey application is presented regularly to a supervising physician via the Web-based backend interface used for monitoring treatment and toxicity and preparing for regular patient visits. Routine check-up visits are conducted once weekly, and additional visits are arranged as requested by the patients via the app. The number and length of all visits are documented. The app-based therapy support is continued daily as long as the patient is in outpatient care.

The standard of care outside this trial at our institution for patients undergoing outpatient radiotherapy consists of weekly scheduled visits with a supervising physician and bloodwork at an interval depending on diagnosis (usually once weekly or less). The therapy support provided within this trial represents an additional, more close-knit and individualized form of care during radiotherapy.

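### Admission for toxicity is both a secondary endpoint and a predictor in the model applied to the secondary endpoints; as an event during therapy it is also not a patient characteristic

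*Protocol article*

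**What the plan says.** In the protocol article, the Statistical Analysis section gives the purpose of the regressions: "multivariable regression models will be used to analyze the relationship between patient characteristics and the primary endpoint". The outcome is the share of questions answered, kept on its continuous scale, and "thus, linear regression models will be applied". The predictors are then fixed, and the next sentence extends the model: "Age, gender and the need of toxicity-caused hospitalization will be included as predictors. The same model will be applied for the secondary endpoints".

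The section Assessment of Primary and Secondary Endpoints lists five secondary endpoints: satisfaction, number of consultations, duration of consultations, admission for toxicity, and health-related quality of life. The fourth is the same variable as the third predictor.

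Study Design places admission in time: "the necessity of admitting a patient to inpatient care during the course of therapy will be documented together with the timepoint of admission". That section also plans an exploratory correlation screen for factors that predict inpatient admission, so there admission is an outcome.

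**The concern.** There are two separate problems.

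- **Circularity.** One variable stands on both sides of the equation for one secondary endpoint. That analysis cannot show how age or gender relates to admission, although it is planned for that endpoint.
- **Mismatch with the stated aim.** The regressions are meant to relate patient characteristics to the outcomes. Admission for toxicity arises after treatment has begun. With it in the model, the age and gender coefficients compare patients of the same admission status. That differs from asking how older and younger patients, or men and women, differ in app use, satisfaction or quality of life.

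At stake is how these secondary results are read and carried into the larger studies that the trial is meant to prepare. The feasibility decision itself is not at stake.

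**Working it through.** **1. The plan's own figure, as background.** The inputs are "With a sample size of 50 patients in this pilot study and an assumed percentage of 92% for the primary endpoint", a null proportion of 80% and a one-sided level of 5%. The smallest r with P(X ≥ r | 50, 0.80) ≤ 0.05 is r = 45 (0.0480; r = 44 gives 0.1034). Power is P(X ≥ 45 | 50, 0.92) = 0.792, which agrees with the stated 80% to within one percentage point. Nothing in this calculation uses the regression model.

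**2. The model for admission.** Let h be 1 if the patient was admitted for toxicity and 0 otherwise. The section as written gives

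h = b0 + b1·age + b2·gender + b3·h + error.

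Setting b0 = b1 = b2 = 0 and b3 = 1 makes every residual exactly 0. No other fit can have a smaller sum of squares, and the solution is unique as long as h is not a linear combination of the constant, age and gender. So R-squared = 1 and the age and gender coefficients are 0, whatever the data. A numerical check with n = 50 and simulated covariates gave this result at assumed admission rates of 10% (5 patients) and 20% (10 patients).

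**3. The other models.** For any outcome y, least squares obeys an exact identity:

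age coefficient without h = age coefficient with h + (coefficient of h) × d,

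where d is the age coefficient in a regression of h on age and gender. The two age coefficients agree only if admission is unrelated to the outcome given age and gender (coefficient of h = 0), or unrelated to age given gender (d = 0). The documents give no figures for either quantity.

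An illustration with assumed effects only: n = 50; age standardised; log-odds of admission −2 + 0.8·age; y = −0.2·age − 1.0·h + standard normal error; 4,000 repetitions. The mean age coefficient was −0.29 without h and −0.20 with h. The gap, −0.29 − (−0.20) = −0.09, is the part of the age association that runs through admission in this set-up. It shows the mechanism and does not estimate what this trial will find.

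**4. How many patients inform the admission coefficient.** The protocol states no admission rate. If 5% to 10% were admitted (assumption), that is 0.05 × 50 = 2.5 to 0.10 × 50 = 5 patients. In every model the coefficient of h would rest on those few. In a model with admission as the outcome, they would be all the events available.

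**The case against.** The case on the other side is substantial, and much of it stands.

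- **The primary analysis does not depend on this.** It is the exact binomial test. Secondary outcomes are first assigned to descriptive methods, the regressions come as an addition, and the trial is an exploratory pilot. This stands and sets the weight of the point.
- **The self-regression would be noticed at once.** An R-squared of 1 misleads nobody, and the authors may have meant the same covariates minus the outcome. That is plausible, but the text does not say it, and it would not answer the second problem.
- **A reader might infer that all coefficients are uninterpretable.** The documents do not support this. Outside the admission model they remain valid as associations conditional on admission. There is one arm, so no treatment effect can be biased. Whether admitted patients answered fewer questions or were less satisfied is a fair descriptive question. What fails is the match with the stated aim.
- **A reader might infer that admission mechanically lowers the share of questions answered**, because "The app-based therapy support is continued daily as long as the patient is in outpatient care". This does not follow. The outcome is a proportion, and the primary endpoint counts questions during outpatient radiotherapy. If the regression outcome uses the same window, fewer outpatient days make a patient's proportion less precise but do not by themselves change its level. The sentence also does not say whether app use resumes after discharge.
- **Admission is already screened as an outcome.** The correlation screen in Study Design covers inpatient admission in general and is described there as a side analysis. It neither removes admission from the predictor list nor gives the secondary endpoint a workable model.

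**Conclusion.** The point holds in two parts. First, as written, the model for admission for toxicity is degenerate. This is exact and rests on no assumption beyond reading the predictor list and its extension to the secondary endpoints literally. Second, in the models for the share of questions answered and for the remaining four secondary endpoints, age and gender are adjusted for an event during therapy. Their coefficients therefore do not give the stated relationship with patient characteristics. The direction and size of that shift cannot be derived from the documents.

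This is a rule that the article states, not a detail left to an analysis plan. It should be corrected before analysis, but it concerns secondary, exploratory results only. A reader might infer that the feasibility conclusion or the sample size is in doubt; neither is.

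**What to change.** Change the predictor sentence and the one after it in Statistical Analysis, to this effect:

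- Restrict the predictors to baseline variables: age and gender. Target site (thoracic or pelvic) may be added. It is likely to correlate with gender at n = 50, because breast tumours are thoracic while prostate and gynaecological tumours are pelvic, and subgroup analyses by tumour type are already planned. It is optional for these reasons.
- Apply that predictor set to the other four secondary endpoints.
- Analyse admission for toxicity only as an outcome: descriptively, as number and percentage, or with a model suited to a sparse binary variable, such as penalised logistic regression. Simply deleting it from its own predictor list would still leave a linear model for a yes/no endpoint.
- If admission is kept in any other model, report that model separately as a descriptive association.

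Adding Karnofsky score is not part of this fix. The article mentions it only as an eligibility threshold and does not list it in the assessment schedule.

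The cost is a rewording of two sentences, with no new data and no change to the primary test or the sample size. The one loss is that the adjusted association with admission is no longer part of the main regression.

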**Methods:**

The present single-center, prospective, exploratory trial, conducted at Heidelberg University Hospital, assesses the feasibility of integrating an app-based approach into patient-care during radiotherapy. Patients undergoing curative radiotherapy for thoracic or pelvic tumors will be surveyed regarding general performance, treatment-related quality of life (QoL) and symptoms, and their need to personally consult a physician by means of a mobile app during treatment. The primary endpoint of feasibility will be reached when 80% of the patients have successfully answered 80% of their respective questions scheduled for each treatment day. Furthermore, treatment-related patient satisfaction and health-related QoL is assessed by the Patient Satisfaction Questionnaire Short Form (PSQ-18) and the European Organization for Research and Treatment of Cancer (EORTC) questionnaires at the beginning (baseline) and end of radiotherapy, and at the first follow-up.

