Based on the promising preliminary results of a systematic survey being conducted at Heidelberg University Hospital among a large number of cancer patients demonstrating a high acceptance of mobile app–based measures of therapy support, the present OPTIMISE-1 trial (which stands for **O**ncologic Thera**p**y Suppor**t** V**i**a **M**eans of a Ded**i**cated Mobile App – A Pro**s**pective F**e**asibility Evaluation) aims to assess the feasibility of introducing a mobile app to the treatment schedule of patients undergoing radiotherapy, as well as measuring its impact on patient satisfaction and health-related quality of life (QoL).

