Health-related QoL is assessed by the EORTC QLQ-C30 questionnaire in addition to the diagnosis-specific questionnaire module (eg, BR23 for breast cancer or PR25 for prostate cancer). Patients are prompted to fill out these questionnaires prior to the initiation of radiotherapy, at the time of treatment completion and at the first follow-up visit, which is routinely scheduled at 6-8 weeks after the completion of therapy. The duration and number of all visits during radiotherapy is documented to estimate the average cost of this form of therapy support. Per our SOP, the beginning and end of every consultation for all patients is documented by the physician by setting status flags within the Radiation Oncology Clinic Information System (ROKIS). The duration of every consultation can then be extracted by querying the ROKIS database. The software solutions in use for those purposes at our institution are MOSAIQ (ELEKTA, Stockholm, Sweden) for ROKIS and Crystal Reports (SAP, Walldorf, Germany) for generating database reports.

Table 1 shows the intervention and assessment schedule for the trial. The Standard Protocol Items: Recommendations for Interventional Trials (SPIRIT) checklist [12] on different protocol items related to this trial is included in Multimedia Appendix 1.

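### The stated regression for health-related QoL leaves out the pre-radiotherapy QoL score that the trial collects; adding it would make the EORTC models clearer and usually more precise at little cost

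*Protocol article*

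**What the plan says.** The Statistical Analysis section describes multivariable models for the proportion of app questions answered, taken on its original scale. The model type is fixed: "linear regression models will be applied". So are the covariates: "Age, gender and the need of toxicity-caused hospitalization will be included as predictors". The model is then extended: "The same model will be applied for the secondary endpoints".

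Health-related QoL is on the list of secondary endpoints. The section on primary and secondary endpoints says how it is measured: "Health-related QoL is assessed by the EORTC QLQ-C30 questionnaire in addition to the diagnosis-specific questionnaire module". Patients are to complete these forms "prior to the initiation of radiotherapy, at the time of treatment completion and at the first follow-up visit". The Methods paragraph of the abstract agrees, placing QoL "at the beginning (baseline) and end of radiotherapy, and at the first follow-up", and Table 1 ticks the EORTC questionnaires at start of radiotherapy, end of radiotherapy and first follow-up.

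The article nowhere enters the baseline score as a covariate, defines the QoL outcome as change from baseline, or describes a longitudinal model. It also does not say which QoL time point is the regression outcome.

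**The concern.** The covariate list was written for the proportion of questions answered, which has no value before treatment. It is carried over unchanged to QoL, which does. An analysis plan may add detail, but this is not a gap that the article leaves open: it names the predictors and says that the same model is used.

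Two things are at stake.

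- **Interpretation.** The Introduction lists the app's effect on satisfaction and QoL among the trial's aims, so readers will want to know about QoL over the course of treatment. In a model of a post-treatment score without baseline, a gender or age coefficient also carries whatever difference existed before the first fraction. The sample is deliberately mixed (breast, lung, gynecological, prostate and some rectal cancers), so gender is tied to diagnosis and differences at baseline are plausible, although the documents do not report any. The hospitalization coefficient has the same problem if patients who start with poorer QoL are admitted more often, which is plausible but not stated.
- **Precision.** With 50 patients, variation between patients that a collected score could explain is left in the residual.

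**Working it through.** **The plan's own figure.** The only power statement concerns the primary test: n = 50, null rate 0.80, assumed rate 0.92, one-sided 5%, power 80%. The smallest number of successes with exact one-sided error at or below 5% is 45 of 50. Its error is 4.80% and its power 79.2%, which agrees with the stated 80%. The present point does not touch this figure.

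**Inputs for the QoL model**
- From the article: linear regression; three predictors; 50 patients; EORTC scores at baseline, end of radiotherapy and first follow-up.
- Assumed, because the documents give no value: the correlation r between baseline and post-treatment score given the other predictors, taken as 0.3, 0.5 and 0.7; and a baseline gender difference d of 0, 0.3 or 0.5 SD.

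**What the coefficient contains.** Let g be the gender difference in the post-treatment score given baseline. With scores in SD units the slope on baseline is r. Without baseline in the model:

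gender coefficient = g + r × d

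With baseline in the model the coefficient is g. If g = 0:
- r = 0.3, d = 0.3: 0.3 × 0.3 = 0.09 SD (simulated 0.10)
- r = 0.7, d = 0.5: 0.7 × 0.5 = 0.35 SD (simulated 0.36)

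With baseline added, the simulated coefficient is 0.00 to 0.01 in every setting. If d = 0 the two models estimate the same quantity.

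**Residual variance.** Adding baseline multiplies it by about 1 − r²:
- r = 0.3: 1 − 0.09 = 0.91, a fall of 9%
- r = 0.5: 1 − 0.25 = 0.75, a fall of 25%
- r = 0.7: 1 − 0.49 = 0.51, a fall of 49%

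**Standard error of the gender coefficient** (simulation, n = 50, 4,000 runs per setting, SD units; model as written → with baseline):

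| r | d = 0 | d = 0.5 |
|---|---|---|
| 0.3 | 0.294 → 0.283 | 0.287 → 0.287 |
| 0.5 | 0.288 → 0.254 | 0.293 → 0.268 |
| 0.7 | 0.296 → 0.211 | 0.287 → 0.214 |

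The gain for a given coefficient is smaller when that predictor is itself related to baseline, and at r = 0.3 with d = 0.5 it vanishes.

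**Cost in degrees of freedom.** Intercept plus three predictors leaves 50 − 4 = 46; adding baseline leaves 45.

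**The case against.** The strongest reply is that the model as written is not wrong. The section introduces these regressions as a way of relating patient characteristics to the outcome, and the unadjusted association of age or gender with QoL at a time point is a legitimate description. Men and women, or older and younger patients, are not randomised groups, so adjusting for baseline changes the question being asked. The zero in the adjusted model above follows from setting g = 0. In the same simulations with d above 0, an unadjusted change score gives −0.09 to −0.35 SD. None of the three analyses is the only correct one. All of this stands. A reader might infer that the planned age and gender coefficients are biased or spurious, but the documents do not support that: they report no baseline difference and do not declare that change given baseline is the target of these models.

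It also stands that the article does not name the QoL time point, so the point is framed for any post-treatment score. If a change score is intended, baseline would enter through the outcome, but the article does not say so.

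The scope is limited too. Number and duration of consultations and need for hospitalization have no baseline score, so the point does not reach them. For the PSQ-18 the abstract implies a baseline assessment while Table 1 ticks end of radiotherapy only, so it applies there only if a baseline PSQ-18 is actually collected.

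What the reply does not remove is that a relevant score, collected by design, is left out of a model whose predictors are stated.

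**Conclusion.** The concern holds as a minor improvement to a secondary exploratory analysis, for the EORTC QoL scores only. For a post-treatment score, the stated model combines differences present before radiotherapy with change during app-supported therapy. Adding baseline would cut residual variance by about 9% to 49%.

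That range rests on the assumed r of 0.3 to 0.7. The 0.09 to 0.35 SD carried into the gender coefficient rests in addition on an assumed baseline difference of 0.3 to 0.5 SD and is an illustration, not an estimate for this trial. The omission itself is clear from the text.

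The primary exact binomial test, the sample size and its power are unaffected. A reader might also infer that adjustment for baseline would let the trial measure the app's effect on QoL. It would not: there is no comparison group, so change during treatment cannot be attributed to the app with or without the covariate.

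**What to change.** In the Statistical Analysis section, qualify the sentence that extends the model to the secondary endpoints:

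- For each EORTC QLQ-C30 or module score analysed, name the scale and give the outcome time points as end of radiotherapy and first follow-up.
- Keep age, gender and toxicity-caused hospitalization, and add the patient's pre-radiotherapy score on the same scale as a covariate. Alternatively, use one repeated-measures model for the two post-treatment scores with baseline as covariate.
- State that the coefficients are associations given baseline QoL. The unadjusted model can be shown alongside.
- Leave the models for consultations and hospitalization as they are in this respect. Treat the PSQ-18 in the same way as QoL only once the abstract and Table 1 have been reconciled on whether a baseline form is collected.

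The cost is one degree of freedom per model and the loss of patients with no baseline form, whose number should be reported. Module scores exist only for patients with the matching diagnosis, so those models have fewer than 50 patients and the extra term weighs more there. No new data are needed and the sample size does not change.
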